### Planned statistical analysis

2.8

#### Analysis of the primary outcome

2.8.1

The primary analysis will examine the effect of NIATx on PNEP participation, using a generalised linear mixed model with a negative binomial distribution, comparing the implementation and control periods [41]. The model will include intervention status and time (categorical by month) as fixed effects and a random intercept and period effect (months) at the prison level. Fixed effects represent the group-average structure, with inclusion of time separating the secular trend from the intervention effect [60]. Random effects will account for both within- and between-period intra-cluster correlations. A log offset for prison population size will be included to adjust for differences in prison size and so that results represent the rate of participation, rather than a count of participants. The Kenward-Roger degree-of-freedom correction will be used to account for the small number of clusters. The implementation effect estimate will be expressed as a rate ratio with 95% confidence interval, with the significance level set at α = 0.05.

In a secondary, exploratory non-inferiority analysis of the primary outcome, we will compare the post-implementation (maintenance) period to the late implementation period to examine whether effects are sustained once external facilitation ends. As this is an exploratory analysis and the primary outcome was pre-specified, we will not perform a multiplicity adjustment, with the focus on effect estimates and confidence intervals.

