### Overall design

2.3

This protocol follows the StaRI Statement for implementation studies and incorporates relevant items of the CONSORT Statement extension for stepped wedged cluster randomised trials (Appendices A and B) [36,37]. NEXUS is a type 1 hybrid effectiveness-implementation trial designed to increase uptake of the Canadian PNEP among people who inject drugs in prison by addressing barriers to participation. Type 1 hybrid studies focus primarily on measuring the effectiveness of the intervention, and secondarily explore implementation-related factors [38]. They are suitable when there is existing evidence that the intervention is effective in other settings or populations, supporting its applicability to a new context [39].

All nine federal prisons with an established PNEP at the time of the trial were enrolled, comprising five women's prisons (five multi-level security) and four men's prisons (one minimum security, one medium security, one maximum security, and one multi-level security) (Table 1). Using a stepped-wedge cluster design, each prison will transition from standard of care to NIATx activities over the study period. This design incorporates a six-month baseline period of pre-NIATx data collection which serves as the control condition. We chose a cluster design because NIATx targets organisational-level process improvements that cannot be delivered at the individual level. In a stepped-wedge trial, the effect estimate comparing NIATx to standard of care combines both within-cluster (i.e., outcomes before vs. after implementation within the same prison) and between-cluster (i.e., prisons with the intervention vs. without the intervention at a given time) effects [40]. A key challenge in this design is that outcomes may change over time due to factors unrelated to the intervention [41]. Ideally, the order in which each cluster receives the intervention is randomised to mitigate this potential source of bias.

**Table 1 tbl1:** Baseline prison needle exchange program participation and prison population size, September 2024-February 2025.

Group	Prison	Province	Security level	Gender	Sep. 2024	Oct. 2024	Nov. 2024	Dec. 2024	Jan. 2025	Feb. 2025
1	Atlantic Institution	New Brunswick	Maximum	Men	17/247 (6.9%)	14/236 (5.9%)	17/224 (7.6%)	17/225 (7.6%)	18/237 (7.6%)	17/225 (7.6%)
	Dorchester Penitentiary	New Brunswick	Multi	Men	10/350 (2.9%)	10/359 (2.8%)	12/362 (3.3%)	14/369 (3.8%)	13/365 (3.6%)	13/368 (3.5%)

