### Allocation and sequence generation

2.4

Although the nine prisons were initially randomised into three sequences, logistical issues required minor adjustments, with one prison per sequence exchanged to accommodate travel and scheduling restrictions. Potential bias from the lack of randomisation will be considered in the interpretation of results. The three sequences are activated at six-month intervals. Each sequence undergoes pre-implementation activities, consisting of NIATx training conducted in the final three months of the six-month baseline control period, followed by 24 months of NIATx implementation, and 12 months of maintenance (Fig. 2). The study commenced in September 2024, with sequence 1 beginning pre-implementation activities in December 2024.

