#### Implementation phase

2.5.2

A NIATx coach will lead activities during the 24-month implementation phase. The coach, members of the research team, and each prison change team will meet monthly via videoconference to use NIATx tools to guide process improvement. Each month, the change team will plan and implement a change project using a plan-do-study-act framework, tailored to address site-specific barriers identified through nominal group technique, walk-throughs, and/or flowcharting. For example, some may focus on increasing awareness of the PNEP through discussions with new prison admissions, while others may address the lengthy PNEP application process [30,32]. The role of the NIATx coach in this process is to guide rather than direct, building the capacity of each team to sustain process improvements beyond the implementation phase [43]. Key coaching elements include providing encouragement, positive reinforcement, and troubleshooting to reduce frustration and sustain momentum during the change project process [43]. We anticipate some staff turnover during the implementation phase; when this occurs, departing team members will be replaced by staff from the same department (i.e., health or corrections), who will be trained in the NIATx tools.

Developed in collaboration with Correctional Service Canada, a PNEP ‘data dashboard’ will allow change teams to make data-driven decisions following implementation of their monthly change projects. The dashboard is updated monthly and provided to change team members prior to each coaching call. For example, the number of PNEP applications will be tracked over time to evaluate PNEP uptake, while median time to participation approval will be used to understand timeliness of program access. Change teams will review these data monthly to determine whether to adopt, adapt, or abandon the changes implemented through rapid cycling testing. Over the course of the implementation phase, there will be approximately 24 monthly change projects. A NIATx fidelity form is completed after each coaching call.

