#### Power

2.8.3

Power calculations were based on detecting an absolute increase of 5% in PNEP participation, which was considered a realistic and clinically important difference. Estimates were conducted for a fixed sample of nine prisons transitioning over three six-month steps. All model parameters were derived from baseline data from the participating sites (Table 1). Specifically, we incorporated the observed average monthly population of 200 people per prison, a baseline PNEP participation rate of 5%, a within-period intra-cluster correlation coefficient (ICC) of 0.05, and a cluster autocorrelation coefficient (CAC) of 0.95. The correlation structure was modelled with an exponential decay to allow for a different within and between-period ICC. With a two-sided significance level of 0.05, we achieve 95% power to detect a 5% absolute increase (i.e., an increase from 5% to 10%) in PNEP participation. ICC and CAC coefficients were estimated using the ICC Estimation Shiny App [61] and power calculations were performed using the Shiny CRT Calculator [62].

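### The single on/off intervention term underestimates a NIATx effect that builds up over the 24 implementation months: attenuated if build-up is quick, near or below null if it is slow

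*Protocol article*

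**What the plan says.** Section 2.8.1 specifies a negative binomial mixed model, "comparing the implementation and control periods", and reports one rate ratio. Its fixed effects are given as: "The model will include intervention status and time (categorical by month) as fixed effects". Its random part is "a random intercept and period effect (months) at the prison level", which amounts to a nested exchangeable correlation. No lag, transition period or term for time since the switch is stated.

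On timing, section 2.3 says: "This design incorporates a six-month baseline period of pre-NIATx data collection which serves as the control condition". Section 2.4 says: "The three sequences are activated at six-month intervals". After its control period each sequence is "followed by 24 months of NIATx implementation, and 12 months of maintenance". The switches therefore follow study months 6, 12 and 18.

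On delivery, section 2.5.2 says: "Over the course of the implementation phase, there will be approximately 24 monthly change projects". After each one the team decides whether to keep, alter or drop the change.

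On power, section 2.8.3 says: "Estimates were conducted for a fixed sample of nine prisons transitioning over three six-month steps". It claims 95% power for a rise from 5% to 10%, using exponentially decaying correlation.

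The sensitivity analysis in 2.8.2 removes only the training months before the switch. The fidelity and staff-attitude models in 2.8.4 are exploratory and do not model time since the switch.

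**The concern.** In implementation month 1 a prison has had at most its first change project; by month 24 it has had about 24. The outcome is a monthly count of current participants, and entry passes through an application and a security assessment that the protocol itself calls slow. An effect that grows with exposure is therefore plausible, but the primary model has no place for it.

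From study month 19 no prison is in control. Those months inform the on/off term only through the estimated prison effects and correlations. If the effect grows, prisons exposed longer look higher than prisons exposed for less time. With exposure time absent from the model, part of that gap is charged to the prisons and the calendar and taken off the intervention effect. Categorical month does not prevent this, and randomising the order would not have prevented it either.

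At stake is the trial's one confirmatory result. It could understate a programme that works and, if build-up is slow, show no effect.

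**Working it through.** **Inputs.** From the protocol: 9 prisons in 3 sequences; switches after months 6, 12 and 18; 24 implementation months each; 200 people per prison; 5% rising to 10%; ICC 0.05; CAC 0.95; two-sided alpha 0.05. Assumptions: CAC is taken per month in the monthly layout, because the protocol gives no time unit; the binomial variance is averaged over 5% and 10%; a normal test is used.

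**Step 1: reproduce the stated power.** With four six-month periods, exponential decay and one constant effect, generalised least squares (GLS) gives SE = 0.0139. Power = Φ(0.05/0.0139 - 1.96) = Φ(1.64) = 95%. The protocol's figure reproduces. It rests on a full 5-point rise from the first exposed period.

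**Step 2: weights of the on/off estimate.** With monthly periods, the estimate is the intervention row of (XᵀV⁻¹X)⁻¹XᵀV⁻¹y. If the true effect in implementation month s is f(s), the expected estimate is Σ w(s)·f(s), with the weights w(s) summing to 1.

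| Implementation months | Planned random effects | Exponential decay |
|---|---|---|
| 1-6 | +1.051 | +1.319 |
| 7-12 | +0.350 | -0.155 |
| 13-18 | -0.105 | -0.164 |
| 19-24 | -0.296 | 0.000 |
| Sum | 1.000 | 1.000 |

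Equal weighting would give 0.25 per block. Under exponential decay, month 1 alone carries +0.62.

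**Step 3: expected estimate for assumed curves**, as a share of the full effect. For linear build-up over L months, then constant, the true 24-month average is 1 - (L - 1)/48. For a six-month lag it is 18/24.

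| Curve | True average | Exponential decay | Planned random effects |
|---|---|---|---|
| Immediate, constant | 1.00 | 1.00 | 1.00 |
| Over 3 months | 0.96 | 0.51 | 0.83 |
| Over 6 months | 0.90 | 0.24 | 0.56 |
| Over 12 months | 0.77 | 0.07 | 0.18 |
| Over 24 months | 0.52 | 0.03 | -0.04 |
| None for 6 months, then full | 0.75 | -0.32 | -0.05 |

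The last row follows directly from Step 2: 1 - 1.319 = -0.32 and 1 - 1.051 = -0.05.

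**Step 4: direction.** Any effect that never falls is a mixture of steps starting at month k. For every k from 2 to 24, the summed weight from month k onward is below (25 - k)/24, under both structures. So every build-up, not only those in the table, is estimated below its 24-month average.

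**Step 5: robustness.** Varying ICC from 0.01 to 0.20, CAC from 0.80 to 1.0 and the total length, or using only each sequence's own six control months, keeps the 24-month share between -0.10 and +0.06. Log-link Poisson and negative binomial fits, with prison and month effects, to expected counts built from Table 1 (suppressed counts set to 3) agree. A rate ratio rising to 2.0 at month 24 is fitted as 0.95 to 0.96, against a true average of 1.43.

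**Step 6: consequence for power.** If 5 points are reached linearly at month 24, the expected estimate is 5 × 0.025 = +0.1 points (exponential decay) or 5 × (-0.041) = -0.2 points (planned random effects). The chance of a significant increase is then about 3% or 1%.

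**The case against.** The strongest reply is that the harm depends on a curve the protocol never states. About 24 projects are planned, but early gains that level off fit that text too: barriers were ranked beforehand and training precedes the switch. This stands. A reader might infer that the model will report a working programme as null or harmful. The documents do not support that. Build-up complete within 3 to 6 months gives 24% to 83% of the full effect, and an immediate constant effect is estimated without bias.

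Nor is there one fixed pattern of weights. Months 7-12 are positive under the planned random effects and negative under exponential decay, and months 19-24 carry no weight under the latter. What is common to both is more than full weight on months 1-6 and zero or negative weight from month 13.

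A single term with categorical time is a conventional stepped-wedge model, and sensitivity analyses are often left to a SAP, which is not at hand. That tempers the request but does not remove the point: section 2.8.1 fixes the primary model, and no analysis listed in the article guards against build-up.

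It would also be wrong to conclude that the 95% power is miscalculated, since it reproduces. Nor do six-month exposure blocks cure the problem in general. They are exact under exchangeable correlation. Under exponential decay, restricted to study months 1-18, they return 0.15 against a true 12-month average of 0.27 for the 24-month build-up, and 0.40 against 0.79 for the 6-month one.

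Finally, making a 12-month average primary has its own cost. Within study months 1-18, exposure months 7-12 are seen only in the three sequence 1 prisons, with the three sequence 3 prisons as the only concurrent controls, and the order was not random.

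**Conclusion.** The point holds in conditional form. The on/off rate ratio describes the implementation phase without bias if the effect is immediate and constant. Any build-up is underestimated. The loss is partial when build-up takes 3 to 6 months (0.24 to 0.83 of the full effect, against true averages of 0.90 to 0.96). The estimate is near or below null when build-up is slow: 0.07 to 0.18 over 12 months, -0.04 to 0.03 over 24 months, and -0.32 to -0.05 after a six-month lag. Slow build-up is plausible from the protocol's description of delivery but is not stated there.

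The figures rest on GLS approximations at the protocol's ICC and CAC and on assumed curves. The direction does not depend on which of the two correlation structures is used; the size does.

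**What to change.** - In 2.8.1-2.8.2, pre-specify an exposure-time analysis with one effect per month since the switch. This model is estimable on the design and returns the true averages under both correlation structures.
- Report the time-averaged effect over the first 12 and over all 24 implementation months beside the on/off rate ratio.
- State that the on/off result will not be read as no effect or harm if the exposure-time effects show build-up.
- In 2.8.3, state that the 95% power applies only to an immediate, constant effect, and give the precision expected for the averaged effects.

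Whether the averaged effect becomes primary is the sponsor's choice.

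**Cost.** No new data are needed, but precision falls. Under the planned random effects, the SE relative to the on/off model is 0.0075/0.0054, about 1.4 times, for the 12-month average (study months 1-18 only) and 0.0104/0.0054, about 1.9 times, for the 24-month average. Power for 5 points stays above 98%. Under exponential decay the ratios are about 0.0227/0.0112 = 2.0 and 0.0379/0.0112 = 3.4, with power about 60% and 26%. If the CAC of 0.95 refers to six months (0.95^(1/6) = 0.9915 per month), those two powers are about 97% and 58%, so the time unit of the CAC should be stated as well. All of these use a normal test except the 98%, which already uses 7 degrees of freedom. The planned small-sample correction would lower the others.

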### Participants

2.6

All people in the nine prisons who self-report a history of injection drug use are eligible to request participation in the PNEP. Due to ethical and privacy concerns, only aggregate (cluster-period-level) data without individual-level identifiers are available for analysis. Consequently, while this design constitutes an ‘open cohort’ [48], we are unable to track specific individuals over time, so data will be analyzed cross-sectionally despite repeated assessment of some of the same individuals. We anticipate that there will be participant overlap between months, meaning the population composition will remain relatively stable over time.

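### The primary model, on its usual reading, gives a prison's months the same correlation at every lag, while the power section assumes decay; if correlation does decay, the nominal 5% test rejects a true null about 15–34% of the time

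*Protocol article*

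**What the plan says.** All references are to the protocol article.

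- **Analysis of the primary outcome (2.8.1).** A negative binomial mixed model has "intervention status and time (categorical by month) as fixed effects" and "a random intercept and period effect (months) at the prison level". Its purpose is given as: "Random effects will account for both within- and between-period intra-cluster correlations". On small samples: "The Kenward-Roger degree-of-freedom correction will be used to account for the small number of clusters".
- **Power (2.8.3).** "The correlation structure was modelled with an exponential decay to allow for a different within and between-period ICC". The inputs are ICC 0.05, CAC 0.95, 200 people per prison, and 5% rising to 10%. The result is: "With a two-sided significance level of 0.05, we achieve 95% power".
- **Participants (2.6).** Only aggregate data are available, and "data will be analyzed cross-sectionally despite repeated assessment of some of the same individuals". Overlap of participants between months is expected.
- **Sensitivity analyses (2.8.2) and Missing data (2.8.6).** The checks concern the training months and the suppressed counts. No decaying correlation, robust variance or permutation test is named.

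**The concern.** A random prison intercept plus a random prison-month effect, with no further structure stated, is normally fitted with independent month effects. That allows one between-month correlation whatever the lag. Under exponential decay at 0.95 per month, the correlation of the prison effects is 0.95 at lag 1, 0.95^6 = 0.74 at lag 6, 0.95^24 = 0.29 at lag 24 and 0.95^41 = 0.12 at lag 41. The analysis and power sections therefore describe different structures for the same outcome. The recurrence of participants makes decay the more natural of the two.

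In a stepped wedge each prison's control months come early and its implementation months late. Slow drift within a prison therefore looks like an intervention effect. A model that treats whatever the prison intercept leaves over as independent monthly noise counts each extra month as new information and makes the standard error too small. This is the single primary test, with nine clusters and a rollout order that was not kept random. Ordinary drift in a few prisons could be declared an effect of NIATx.

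There is also only one count per prison-month. An independent prison-month effect and the negative binomial dispersion then describe nearly the same extra variance, and neither carries serial correlation.

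**Working it through.** **1. Inputs.** From sections 2.4 and 2.8.3: 9 prisons, 3 sequences, six-month steps, m = 200, ICC = 0.05, CAC = 0.95, 5% to 10%, two-sided α = 0.05, 24 months of implementation. Assumed: three prisons per sequence, all observed from month 1, with implementation starting after months 6, 12 and 18.

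**2. The plan's own power.** Covariance of a prison's period means: V = σ²[ICC·CAC^|lag| + (1 − ICC)/m · I], with σ² = (0.05·0.95 + 0.10·0.90)/2 = 0.06875. With four six-month periods and categorical time, generalised least squares gives SE = 0.0139. Power = Φ(0.05/0.0139 − 1.96) = Φ(1.64) = 95%, which is the stated figure. With 24 monthly periods and 0.95 per month, SE = 0.0112 and power is 99.4%. The 95% therefore fits CAC 0.95 per six-month step, although the text gives no unit. Per month, that is 0.95^(1/6) = 0.9915.

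**3. Type I error.** Prison-month means were generated with no intervention effect and the V above at monthly lags. The fit had month fixed effects, intervention, a random prison intercept and an independent month-level residual (REML linear model, 3,000–4,000 runs per row). With one value per prison-month, the month effect and the sampling noise form one residual.

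Under this fit the intervention effect is estimated within prisons, so the degrees of freedom come from prison-months. For 24 months they are 216 − 24 − 1 − 8 = 183. The t on 7 column is a deliberately conservative alternative.

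Three windows were used: 18 months; 24 months; and 42 months with each sequence cut at the end of its implementation, giving 3·(30 + 36 + 42) = 324 prison-months.

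| Decay | Window (months) | Rejects at nominal 5% | Same, t on 7 df | True SD / model SE |
|---|---|---|---|---|
| 0.95 per month | 18 | 34% | 25.5% | 2.05 |
| 0.95 per month | 24 | 27% | 18% | 1.73 |
| 0.95 per month | 42 | 31% | 23% | 1.96 |
| 0.95 per six months | 18 | 24% | 15% | 1.65 |
| 0.95 per six months | 24 | 15% | 9% | 1.38 |
| 0.95 per six months | 42 | 20% | 13% | 1.54 |

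Repeat simulations agree to within about three percentage points. If maintenance months were also counted as implementation (9 × 42 = 378 prison-months), the 42-month rates would be about 40–42% and 31–33%. The plan does not do this, so those figures are left out of the conclusion.

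**4. Controls.**
- Data generated as block-exchangeable: 4% at both 24 and 42 months. The inflation therefore comes from the mismatch.
- Negative binomial mixed model with log offset, 24 months, 600 runs: 21% at 0.95 per month, 14.5% at 0.95 per six months, 4% under an exchangeable truth.
- Four six-month periods in place of months: 2–4%. The mismatch does harm at the monthly resolution that section 2.8.1 uses, not at the one that reproduces the power.

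**5. After the change.** Fitting a first-order autoregressive prison-month effect plus sampling noise to the same data gives 5–7% with a normal reference and 2–3% with t on 7 df.

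**The case against.** **The text does not say that the month effects are independent.** A prison-level month effect can carry an autoregressive covariance, and an analysis plan that is not shown may specify one. Sections 2.8.1 and 2.8.3 also use similar words about within- and between-period correlation, so one structure may be intended. This stands as far as it goes: a reader might infer that the trial's test certainly has the inflated error, and the document does not establish that. But 2.8.1 does state the random effects, the usual reading has no decay, and the power section shows that decay was thought relevant.

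**Kenward-Roger protects the test.** It adjusts the standard error and degrees of freedom given the fitted covariance. It does not repair a covariance of the wrong form, as the t on 7 column illustrates.

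**Table 1.** A reader might take the very stable counts as proof of decay (variance/mean 0.11 at Atlantic, 0.18 at Mission, 0.23 at Dorchester). They are not proof, because a large constant prison effect gives the same picture. At Atlantic the first and last months are equal (17 and 17) while adjacent months differ. Six months cannot settle the matter.

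**The simulated trial is simpler than the real one.** Five of the nine prisons are suppressed in all six baseline months, and suppressed counts are set to 3. A simulation with Table 1 sizes and that rule (assuming a true mean of 2.5 in suppressed prisons and drift SD 0.2–0.6 on the log scale) gave 7–14% with per-step decay and 12–27% with per-month decay. The inflation is smaller there but remains.

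**Conclusion.** The concern holds in conditional form. Sections 2.8.1 and 2.8.3 do not match, and the primary model on its usual reading does not allow for the decay that the trial itself assumes. If that decay is real, the nominal 5% test rejects a true null about 25–34% of the time with CAC 0.95 per month, and about 15–25% with CAC 0.95 per six-month step. The per-step reading is the one that reproduces the 95% power.

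These figures rest on equal prisons of 200 at 5% uptake, a linear approximation, and an analysis window that the article does not state. The negative binomial fit and the Table 1 simulation give somewhat lower values, and nearly all remain well above 5%.

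A reader might also infer that the standard error is always about half its proper size. That is roughly true only under per-month decay (ratio 1.7–2.0). Under the per-step reading the true SD is about 1.4–1.7 times the model SE.

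**What to change.** In section 2.8.1:

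- Replace the independent month effect with a prison-level first-order autoregressive (exponential-decay) month effect, matching section 2.8.3.
- State the time unit of the CAC in 2.8.3 and the months that enter the primary comparison.
- Keep a small-sample correction.
- Do not add a second independent month-level variance term that duplicates the negative binomial dispersion. This does not imply a conditional Poisson model: the three prisons above have variance below the mean, which that model would fit poorly.
- Apply the same structure to the secondary outcomes in 2.8.5.

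If a decaying structure was intended all along, one sentence saying so settles the point. The cost is that sentence, the model code and a wider confidence interval. No new data are needed.
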